### Study design

#### In silico development

Our study will be conducted across three distinct centers located in Shanghai, Nanjing, and Suqian. The development of the multimodal AI system takes place in Shanghai. We will gather medical dialogues (at least 20 dialogues for each subspecialty) from 10 ophthalmic subspecialties, which include general ophthalmology, refractive diseases, strabismus, cornea, cataract, glaucoma, retina, neuro-ophthalmology, oculoplastics and orbital diseases, and ophthalmic emergencies (Supplementary Tables 1, 2). We will utilize these dialogues for prompt engineering to guide the ChatGPT diagnostic system. The brief process is as follows (Figure 2): When users input their chief complaints, the system will categorize them using a chief complaint classifier. Once classified, the system will automatically generate a tailored question list for the user and output each question from the list. After receiving the user's responses, both the chief complaints and all answers will be consolidated into the diagnostic prompt, which ultimately produces the user's diagnosis and triage results. Once the interactive system is developed, virtual cases (at least 50 cases for each disease) representing the top 1–5 diseases in each subspecialty will be introduced to assess diagnostic efficacy. For the diseases that fail to meet the predefined performance thresholds (sensitivity ≥ 90%, specificity ≥ 95%), we will develop an image-based diagnostic system tailored to the cases that have anterior segment images. Subsequently, we will integrate these components to establish a multimodal AI system, with a primary focus on image-based diagnosis, for the comprehensive evaluation of ophthalmic diseases (Figure 3).

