#### Silent evaluation

The multimodal AI system will be integrated into a mobile mini-program to enable the diagnosis and triage of ophthalmic diseases. This mini-program will undergo a silent evaluation phase, conducted as a cross-sectional study, in Shanghai (STROBE checklist for cross-sectional study is detailed in Supplementary material 1). A team of researchers will collect medical history on the mobile mini-program in outpatient clinics without intervening in the medical inquiry process. For patients who have undergone anterior segment imaging examinations (Supplementary Table 3), the researchers will provide the corresponding anterior segment images and respond to queries generated by the AI system, utilizing information extracted from the medical dialogues. In cases where no relevant information is available for a specific query, the researcher will denote it as “no information available”.

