### Blinding

The blinding methods vary depending on the roles of the researchers and the stage of the study in which the researchers and subjects are involved. AI developers and AI output correctness assessors have access to complete patient information, including medical history, reference standard results, and AI output for determining correctness.

In our study, two roles are subject to blinding. (1) Reference standard assessors: These assessors possess knowledge of the patient's clinical information but are unaware of the AI output or its correctness. This approach helps mitigate information bias and classification bias. (2) Clinical researchers: These researchers are responsible for inputting data into the multimodal AI program. During the *in silico* development stage, they have access to all patient clinical information and reference standard results. However, during the silent evaluation and early clinical evaluation stages, they only have access to the patient's clinical information without knowledge of the reference standard. This approach helps mitigate diagnostic suspicion bias.

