### Implementation

Clinical researchers responsible for AI system input data play a crucial role in influencing the research outcomes. Our implementation strategies focus on training researchers to minimize human-induced confounding bias. In the *in silico* development stage, researchers are required to hold a PhD in Ophthalmology from Fudan University and have at least 3 years of clinical experience as attending physicians. Prior to implementing the study, they must have completed rotational training in various ophthalmic subspecialties to ensure proficiency in medical inquiry, diagnostic criteria, and medical record documentation for common ophthalmic diseases.

During the silent evaluation and early clinical evaluation stages, clinical researchers will be junior university students specializing in clinical medicine at Fudan University. They will receive training in ophthalmology-related terminology and patient communication, enabling them to explain medical terms to patients and provide accurate responses to the AI system's queries. Data collection across the three research sites will be conducted by the same group of researchers.

For anterior segment image captured in medical facility, the technicians should possess a minimum of two years of experience to ensure precise lesion capture with appropriate lighting conditions. The researchers responsible for smartphone-based images should be pretrained to capture clear anterior segment images with smartphones.

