### Sample size calculation

In the *in silico* development stage, the sample size is adjusted based on AI system performance. Initially, each subspecialty involves 20 medical dialogues, with 80% for training ChatGPT and 20% for validation. If ChatGPT cannot generate inquiries, diagnoses, and triage results in the validation dataset, we'll increase the dialogues. Next, 50 virtual cases for the top 1–5 diseases in each subspecialty are input into the diagnostic system. If the sensitivity and specificity of specific diseases do not meet the predefined thresholds (sensitivity ≥ 90%, specificity ≥ 95%), we will proceed to develop a disease-specific image-based diagnostic system. For each disease, we will compile a dataset consisting of 50 cases, including both anterior segment images and their corresponding diagnoses. This dataset will be randomly partitioned into training and testing sets, with the training set supporting system development and the testing set assessing diagnostic accuracy. Should the predetermined criteria (sensitivity ≥ 90%, specificity ≥ 95%) be satisfied, there will be no necessity for further expansion of the sample size.

For the silent evaluation stage, the primary objective is to achieve a sensitivity ≥ 85% and specificity ≥ 95% for diagnosing ophthalmic diseases. To meet this goal, we set sensitivity = 0.85, specificity = 0.95, statistical power (1-β) = 85, significance level (α) = 0.05, and the sample size for each disease is determined to be 22, following the methodology (Tests for One-Sample Sensitivity and Specificity) outlined in Pass15. Since this stage covers at least four different illnesses, we will include a minimum of 88 patients in the entire sample. To account for potential confounding factors, we have opted to include 100 patients in this phase.

For the early clinical evaluation stage, all subjects collected within predefined date ranges at three sites will be included. Data collection at the Shanghai and Nanjing sites spans from July 21 to August 20, 2023. At the Suqian site, data collection is scheduled from August 21 to August 31, 2023.

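### In the in silico stage the researchers entering the cases hold the reference diagnosis, which leaves the 90%/95% result, and the image-development decision based on it, open to upward bias

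*Protocol article*

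**What the plan says.** All references are to the protocol article.

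- **Blinding** lists two roles as subject to blinding. One is the clinical researchers: "These researchers are responsible for inputting data into the multimodal AI program". For the in silico stage it states that "they have access to all patient clinical information and reference standard results". For the silent and early clinical evaluations it states that "they only have access to the patient's clinical information without knowledge of the reference standard", and gives the reason: "This approach helps mitigate diagnostic suspicion bias".
- **Hypotheses** sets a primary goal for the in silico stage: sensitivity of at least 90% and specificity of at least 95% for diagnosis.
- **In silico development** describes an interactive text system. It classifies the chief complaint and generates a question list, after which "both the chief complaints and all answers will be consolidated into the diagnostic prompt". At least 50 virtual cases per disease then test it. Diseases that miss the thresholds go to image development, for cases that have anterior segment images.
- **Sample size calculation** repeats the rule with 50 virtual cases per disease: "If the sensitivity and specificity of specific diseases do not meet the predefined thresholds", a disease-specific image system is developed.
- **Silent evaluation** covers queries that the consultation did not answer: "In cases where no relevant information is available for a specific query, the researcher will denote it as" having no information available. No such rule is stated for the in silico stage.
- **Implementation** says that those who enter data can strongly influence the outcomes. Its in silico safeguard is qualification and training: "researchers are required to hold a PhD in Ophthalmology from Fudan University", with at least 3 years of clinical experience as attending physicians.

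**The concern.** The typed answers are the input to the index test. When the system asks something that the case text does not settle, the person typing has room for judgement, and at this stage that person has been given the diagnosis. An answer consistent with the known diagnosis would raise apparent performance without any improvement in the system. The article recognises this hazard, since it blinds the same role in the two later stages and says why.

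Two things are exposed. One is the in silico primary result. The other is the decision on image development. A disease that meets the text thresholds only because of informed answers would not be sent for an image module, even where suitable anterior segment images exist. It would then go into the silent and early clinical evaluations on text alone, operated by students who do not know the reference standard. Blinding in those stages does not reopen the decision.

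**Working it through.** The 90% and 95% are targets and not results of a calculation, so there is no stated figure to reproduce. The check has two parts.

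**1. The passages side by side**

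| Item | In silico | Silent and early clinical |
|---|---|---|
| Person entering data knows the reference standard | Yes, stated (Blinding) | No, stated (Blinding) |
| Sensitivity and specificity targets for diagnosis | 90% / 95% (Hypotheses) | 85% / 95%, then 75% / 95% (Hypotheses) |
| Result decides on image development | Yes (In silico development; Sample size calculation) | Not stated |
| Rule for queries without an answer | None stated | Stated for the silent evaluation |

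Access to the diagnosis is therefore an explicit rule, and it applies at a stage with a stated performance goal and a stated consequence. The Blinding section does not separate the cases used to build prompts from the cases counted toward the thresholds.

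**2. How sensitive the threshold is to operator influence (illustration)**

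Inputs:
- n = 50 virtual cases per disease (Sample size calculation).
- Sensitivity threshold 90%, so at least 0.90 × 50 = 45 cases must be correct.
- True text sensitivity p = 0.80 or 0.85. This is assumed.
- f, the share of would-be misses turned correct by an informed operator, = 10%, 25% or 50%. This is assumed; the documents give no value.

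Formulas:
- Apparent sensitivity: q = p + f(1 − p).
- Chance of meeting the sensitivity threshold: P(X ≥ 45) = Σ C(50, k) q^k (1 − q)^(50 − k), summed over k = 45 to 50.

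Example: for p = 0.85 and f = 0.25, q = 0.85 + 0.25 × 0.15 = 0.8875, and P(X ≥ 45) = 50.1%.

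| True sensitivity p | f = 0 | f = 10% | f = 25% | f = 50% |
|---|---|---|---|---|
| 0.80: apparent q | 0.80 | 0.82 | 0.85 | 0.90 |
| 0.80: chance of ≥45/50 | 4.8% | 9.3% | 21.9% | 61.6% |
| 0.85: apparent q | 0.85 | 0.865 | 0.8875 | 0.925 |
| 0.85: chance of ≥45/50 | 21.9% | 31.6% | 50.1% | 83.0% |

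These are chances of meeting the sensitivity half only. Specificity of at least 95% is also required and is not modelled, so they are not probabilities that a disease passes the whole rule.

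**The case against.** The strongest reply is that the harm rests on silence. The article states that operators have the diagnosis. It nowhere says that they fill unanswered questions from it, only that virtual cases are input. The full protocol may fix the answers beforehand. This stands, and it rules out a reading that a reader might infer, namely that the in silico figures are shown to be biased. They are open to bias. The reply does not remove the point, because access to the reference standard is itself a stated rule that the article reverses for the same role later.

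Second, a reader might infer that the evaluation-stage results are inflated. The documents do not support that. Operators in both later stages are blinded to the reference standard, so a disease wrongly passed on text would tend to do worse there and show the problem. Image development is also limited to cases with anterior segment images, so a false pass does not always cost a module.

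Third, hiding the label may achieve little on its own. An experienced ophthalmologist can often guess the diagnosis from a case built to represent a common disease, and the case's author presumably knows it. This is fair. A rule to answer only from the text does most of the work, and masking adds to it.

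Fourth, larger effects can be had by assuming larger flips. At a true sensitivity of 0.85, correcting 10% of all cases gives q = 0.95 and a pass chance of 96.2%. That would require 0.10 / 0.15 = 67% of misses to be rescued, which nothing in the documents supports.

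Finally, a reader might extend the point to the held-out dialogues. The Sample size calculation uses those only to see whether the system can generate inquiries, diagnoses and triage results, and sets no accuracy threshold for them. The image test set does carry the thresholds, but typed answers have little room to act there.

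**Conclusion.** The concern holds in a limited form. The article gives the people entering in silico cases the reference standard, at a stage with its own 90%/95% primary goal and with a decision on image development attached. It does so against its own reason for blinding that role later. The in silico figures and the decision are open to upward bias. The later stages are affected only indirectly, through which diseases, among those with anterior segment images, receive an image module.

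The size is unknown. Under the assumed shares of 10% to 50% of misses turned correct, the chance of meeting the sensitivity half moves from 21.9% to between 31.6% and 83.0% at a true sensitivity of 0.85, and from 4.8% to between 9.3% and 61.6% at 0.80. This rests on the assumed shares and true sensitivities, on independent cases, and on exactly 50 cases per disease. It is an inexpensive improvement worth making. It does not undermine the evaluation stages.

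**What to change.** Amend the Blinding section for the virtual cases counted toward the 90%/95% thresholds:

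1. Answers to the system's queries come only from the prewritten case text. Where the text gives no answer, the operator records that no information is available, as in the silent evaluation.
2. Where existing staffing allows, each case is entered by a researcher who did not write it and does not see its diagnosis or triage label.
3. If entry stays unmasked, the in silico figures are reported as development results from unmasked entry.

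Unmasked entry may stay for prompt-building. The held-out dialogues need no change.

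The cost of items 1 and 3 is protocol wording. Item 2 means exchanging cases between researchers. The article does not say how many work on this stage, so that item is conditional on staffing. The downside is that the in silico figures may come out lower and more diseases may go to image development.

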### Implementation

Clinical researchers responsible for AI system input data play a crucial role in influencing the research outcomes. Our implementation strategies focus on training researchers to minimize human-induced confounding bias. In the *in silico* development stage, researchers are required to hold a PhD in Ophthalmology from Fudan University and have at least 3 years of clinical experience as attending physicians. Prior to implementing the study, they must have completed rotational training in various ophthalmic subspecialties to ensure proficiency in medical inquiry, diagnostic criteria, and medical record documentation for common ophthalmic diseases.

During the silent evaluation and early clinical evaluation stages, clinical researchers will be junior university students specializing in clinical medicine at Fudan University. They will receive training in ophthalmology-related terminology and patient communication, enabling them to explain medical terms to patients and provide accurate responses to the AI system's queries. Data collection across the three research sites will be conducted by the same group of researchers.

For anterior segment image captured in medical facility, the technicians should possess a minimum of two years of experience to ensure precise lesion capture with appropriate lighting conditions. The researchers responsible for smartphone-based images should be pretrained to capture clear anterior segment images with smartphones.

### Statistical analysis

To assess the AI system's diagnostic and triage performance, we will use the one-vs.-rest strategy and calculate the area under the receiver-operating-characteristic curve (AUC), sensitivity, specificity, accuracy, positive predictive values and negative predictive values for disease diagnosis and subspecialty triage using IBM SPSS Statistics 26 software. Specifically, sensitivity measures the AI system's ability to correctly identify positive cases, such as diagnosing a specific disease or assigning a patient to the correct subspecialty. It is calculated by determining the ratio of true positives (correctly identified positive cases) to the sum of true positives and false negatives (missed positive cases). Conversely, specificity evaluates the AI system's capacity to accurately identify negative cases. For instance, it assesses the system's ability to correctly exclude the presence of a particular disease or to avoid assigning a patient to an incorrect subspecialty. Specificity is determined by calculating the ratio of true negatives (correctly identified negative cases) to the sum of true negatives and false positives (incorrectly identified negative cases). Accuracy, which indicates the proportion of correct classifications made by the AI system, will be determined as follows: Accuracy = (True positive + True negative)/(True positive + True negative + False positive + False negative). This parameter offers an overarching evaluation of the system's ability to make precise diagnoses and triage assignments. In addition to sensitivity, specificity, and accuracy, we will also calculate AUC, positive predictive values and negative predictive values. These parameters collectively provide a comprehensive assessment of the AI system's diagnostic and triage capabilities, ensuring a thorough evaluation of its performance. Subgroup analyses will be performed to explore the influence of lesion location (anterior segment disorders vs. posterior segment disorders) on the performance of the multimodal AI system. A *post-hoc* power calculation will also be conducted to assess how lesion locations influence the AI system's performance.

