### Hypotheses

For *in silico* development, our primary goal is to achieve a sensitivity of ≥90% and a specificity of ≥95% for diagnosing ophthalmic diseases. As a secondary outcome, we expect a positive predictive value of ≥90% and a negative predictive value of ≥95% for subspecialty triage of ophthalmic diseases.

For silent evaluation, the primary outcome is to achieve a sensitivity ≥ 85% and specificity ≥ 95% for diagnosing ophthalmic diseases. The secondary outcome is to achieve a positive predictive value ≥ 85% and a negative predictive value ≥ 95% for subspecialty triage of ophthalmic diseases.

For early clinical evaluation, we anticipate the primary outcome to reach a sensitivity ≥ 75% and specificity ≥ 95% for diagnosing ophthalmic diseases. For the secondary outcome, we expect a positive predictive value of ≥80% and a negative predictive value of ≥95% for subspecialty triage of ophthalmic diseases.

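### One-vs.-rest accuracy is presented as the overall measure of correctness, but with many classes it overstates the share of patients diagnosed or triaged correctly; the ≥95% specificity and NPV targets add little for the same reason

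*Protocol article*

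**What the plan says.** The Statistical analysis section fixes the approach for both diagnosis and triage: "we will use the one-vs.-rest strategy and calculate the area under the receiver-operating-characteristic curve (AUC), sensitivity, specificity, accuracy", followed by the predictive values. It gives the formula "Accuracy = (True positive + True negative)/(True positive + True negative + False positive + False negative"), says that this is the share of classifications the system gets right, and adds: "This parameter offers an overarching evaluation of the system's ability to make precise diagnoses and triage assignments". Specificity is defined in the usual way: "Specificity is determined by calculating the ratio of true negatives (correctly identified negative cases) to the sum of true negatives and false positives".

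The Hypotheses section sets paired targets at each stage. For diagnosis in the silent evaluation, "the primary outcome is to achieve a sensitivity ≥ 85% and specificity ≥ 95% for diagnosing ophthalmic diseases"; in the early clinical evaluation, "a sensitivity ≥ 75% and specificity ≥ 95% for diagnosing ophthalmic diseases"; in development, 90% and 95%. For triage, PPV targets of 90%, 85% and 80% are each paired with an NPV target of 95%, for example "a negative predictive value of ≥95% for subspecialty triage of ophthalmic diseases". Accuracy has no target.

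The Outcome measure section makes the primary outcome the correctness of the diagnosis and the secondary outcome the correctness of triage. Each result is judged correct or incorrect against the expert panel, and giving no result counts as incorrect.

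**The concern.** The stated outcome is a judgement per patient: was this patient's diagnosis right? Its natural summary is patients correct divided by patients analysed. The Statistical analysis section lists no such figure. The quantity it calls accuracy is computed within each disease-versus-all-others table, where a wrong diagnosis costs one false negative in one table and one false positive in another, and remains a true negative in all the rest. The more classes there are, the closer the average comes to 100%, whatever the share of patients served correctly.

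Two things are at stake. A reader told that accuracy is the overall evaluation would take a figure of 90% or more as the share of patients diagnosed correctly, when that share could be about half. And specificity and NPV of at least 95%, listed beside sensitivity and PPV, look like separate evidence although they add little to it.

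**Working it through.** **Inputs.** Triage has 10 subspecialties (In silico development). The diseases tested in development are those "representing the top 1–5 diseases in each subspecialty", so 10 × 1 = 10 to 10 × 5 = 50. The silent evaluation is sized on four or more illnesses (Sample size calculation). The number of diseases finally analysed is not given, so K = 4 to 50 is shown. Assumption throughout: one label per patient. The plan states no accuracy figure that could be reproduced.

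**Accuracy.** Let N patients fall into K classes, with a share *a* correctly labelled. The K tables hold NK entries in total. Each wrong patient produces two wrong entries, so

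mean accuracy = 1 − 2(1 − a)/K.

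This holds for any case mix when the K tables are averaged.

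**Specificity and NPV.** With balanced classes, each table has N(K−1)/K negatives and N(1−a)/K false positives on average. With errors spread evenly, the false negatives and the predicted negatives have the same sizes, so

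mean specificity = mean NPV = 1 − (1 − a)/(K − 1).

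**A small example.** Take 100 patients, 10 classes of 10, half correct, errors spread evenly. Each table has TP 5, FN 5, FP 5, TN 85. Accuracy is 90/100 = 90%. Specificity and NPV are both 85/90 = 94.4%. Sensitivity and PPV are both 5/10 = 50%.

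| K | Mean accuracy at a = 50% | Mean specificity at a = 50% | Smallest a for mean specificity ≥95% |
|---|---|---|---|
| 4 | 75% | 83.3% | 85% |
| 10 | 90% | 94.4% | 55% |
| 20 | 95% | 97.4% | 5% |
| 50 | 98% | 99.0% | 0% (from K = 21) |

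**What specificity adds to sensitivity.** In the balanced case, mean specificity is at least 95% when K ≥ 1 + (1 − a)/0.05. Putting in the sensitivity targets:
- 90%: 1 + 0.10/0.05 = 3 classes
- 85%: 1 + 0.15/0.05 = 4 classes
- 75%: 1 + 0.25/0.05 = 6 classes

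Development has at least 10 diseases and the silent evaluation at least 4, so at both stages meeting the sensitivity target already delivers the specificity target on average.

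**Triage NPV.** With ten equal subspecialties, 1 − (1 − a)/9 ≥ 0.95 requires a ≥ 55%. A subspecialty with share p that is never assigned has NPV = 1 − p, so it meets 95% automatically when p ≤ 5%.

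**Non-answers.** A missing result adds one false negative and no false positive. A system that never answered would have specificity 100% and mean accuracy 1 − 1/K, which is 90% at K = 10, although every patient counts as incorrect under Outcome measure.

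**The case against.** A reader might infer that a system that is usually wrong could be declared a success, so that the targets do not test the AI at all. The documents do not support that.

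- **The targets are joint.** Specificity is always paired with sensitivity, and NPV with PPV. With one label per patient, a system wrong for more than half of patients has case-mix-weighted sensitivity below 50% and fails 75%, 85% and 90%. In the balanced case with evenly spread errors its PPV is also below 50%.
- **Accuracy has no target**, so no success claim rests on it. It is also listed as one of several measures to be read together.
- **NPV is weak but not empty.** At 50% correct with ten equal subspecialties it is 94.4%. A random search over unequal ten-class tables with under half of patients correct found a best mean NPV of 94.8%.
- **With four illnesses**, specificity of 95% needs 85% correct. That is a real hurdle, though it is the same one the sensitivity target sets.
- **Specificity can bind for a single disease or with multiple labels.** With 10 classes and 85% correct, if all errors from the other classes go to one class, that class has specificity 85%. If outputs may name several diseases, which the partial-overlap rule in Outcome measure allows for, specificity penalises over-calling: at K = 30, the right disease plus two others gives 27/29 = 93.1%.

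It can also be said that, with single labels, sensitivity pooled over classes equals the share of patients correct, so the needed figure is nearly there already. That is true, but the article does not name it. It names a different quantity as the overall measure.

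All of these points stand. They limit the concern to how accuracy is described and how much weight specificity and NPV can bear. They do not rescue the description of (TP+TN)/all.

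**Conclusion.** The point holds in a limited form. The Statistical analysis section misdescribes one-vs.-rest accuracy: it is not the per-patient correctness that Outcome measure defines, and with half of patients wrong it averages 75%, 90% and 98% at 4, 10 and 50 classes. In the balanced case the specificity target adds little beyond the paired sensitivity target, and the triage NPV target is a low bar: about 55% correct with ten equal subspecialties, and automatic for one with a share of 5% or less that is never assigned. The stage goals as a whole remain a real test through sensitivity and PPV.

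The accuracy result rests on one label per patient. The mean specificity and NPV results also need balanced classes, and the NPV result evenly spread errors; so does the 0%-correct entry in the table as a statement about each single disease. The number of classes actually analysed is not stated, which is why a range is given.

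**What to change.** In Statistical analysis, replace (TP+TN)/all as the overall measure with patient-level accuracy, reported separately for diagnosis and for triage: patients judged correct under Outcome measure divided by all analysed patients, non-answers counted as incorrect, with an exact 95% confidence interval. Add macro-averaged sensitivity across diseases and across subspecialties, so that common classes do not hide poor results in smaller ones.

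Keep one-vs.-rest accuracy, specificity and NPV as per-class descriptive figures. Show each with that class's share of patients, since the Limitation section itself expects disease proportions to differ between centres, and do not offer them as stand-alone evidence of performance.

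The change needs no new data, because the correct/incorrect judgement is already made for every patient, and it leaves the stated targets as they are. The cost is some rewording, a few more lines of output, and less favourable reported figures.
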